## Abstract

**Introduction:**

Surgical site infection (SSI) is the most common complication following major gastrointestinal surgery, affecting between 25% and 40% of patients. The rate of SSI doubles from low-income to high-income settings, persisting after risk adjustment. The relative impact of antibiotic-resistant organisms and the effectiveness of antibiotic prophylaxis globally are unknown. This study aims to determine SSI rates following gastrointestinal surgery across worldwide hospital settings.

**Methods and analysis:**

This multicentre, international, prospective cohort study will be undertaken by any hospital providing emergency or elective gastroenterological surgical services. Centres will collect observational data on consecutive patients undergoing emergency or elective gastrointestinal resection, cholecystectomy or appendicectomy during a 6-month period. The primary outcome is the incidence of SSI with secondary outcomes describing the organisms causing SSIs, including their antibiotic susceptibility, and the microbiological tests used to identify them.

**Ethics and dissemination:**

This project will not affect clinical practice and has been classified as clinical audit following research ethics review. The protocol will be disseminated through the international GlobalSurg network.

**Trial registration number:**

NCT02662231.

Strengths and limitations of this studyThis will be the first international, multicentre, prospective study to assess the incidence of surgical site infections (SSI) for patients undergoing elective and emergency major gastrointestinal surgery.The collaborative methodology adopted, as described elsewhere, allows for large volume, high-quality data collection while avoiding overburdening high-volume and low-resource centres that may otherwise be unable to participate in such projects.Previous studies have had varying subjective definitions of SSI; this study uses standardised definitions from the Centre for Disease Control and Prevention, which are widely implemented and internationally validated.Due to the observational nature of the study, it will not be possible to determine a causative link between risk factors and SSI and therefore comparisons of incidence and risk factors across different Human Development Index settings will be hypothesis generating only.As it is not possible to apply strict data monitoring within the confines of this study, we have developed a mixed-methods quantitative and qualitative validation process for our primary outcome measure, and case ascertainment rate, which will be applied to a sample of representative centres.

## Introduction

The burden of surgical disease in low and middle-income countries (LMICs) is growing.^1^ Specific programmes have aimed to highlight the unmet need for safe surgery and anaesthesia as part of the global health agenda.^2^ The Lancet Commission on Global Surgery outlined six core indicators for the assessment of global surgical systems, including the postoperative mortality rate (POMR).^3^ While clearly important, mortality only affects 1%–4% of all patients.^4^ For major gastrointestinal surgery, quantifying POMR alone neglects the burden of postoperative morbidity, which affects a greater proportion of patients.^2^ Other relevant markers of postoperative outcome are also needed to determine the success of surgery in the majority of patients who will survive.

Surgical site infection (SSI) is the most common complication following major gastrointestinal surgery,^5^ affecting between 25% and 40% of patients after midline laparotomy in high-income settings.^6 7^ SSI is implicated in one-third of postoperative deaths and accounts for 8% of all deaths caused by a nosocomial infection.^8–10^ Furthermore, SSIs cause pain and discomfort, increase hospital stay and put patients at greater risk of secondary infectious complications. This has an important economic impact with an attributable cost in the UK of £30 million per year.^11^

Our 2014/2015 prospective, observational cohort study (GlobalSurg 1^12^) included 10 475 patients from 58 countries. It showed that the incidence of SSI more than doubled from high (7.4%), to middle (14.4%), to low (20.0%)-income countries. This persisted after multivariable risk adjustment for patient and hospital confounders (middle income: OR 1.96 (1.63–2.32) and low income: OR 2.06 (1.67–2.57)). In the most contaminated procedures, one in three patients from LMICs suffered an SSI. Dirty surgery doubled in low-income countries (29.7% vs 16.6% in high-income settings), which was in turn associated with doubling of SSI (34.5% low income vs 15.4% high income). However, SSI was assessed as a secondary outcome measure as part of that study, lacking validity and requiring external validation.

Antibiotic-resistant organisms are now prevalent worldwide and a focus of interest for policy leaders and global health advocates.^13^ In high-income settings, methicillin-resistant *Staphylococcus aureus* accounts for up to 50% of *S. aureus* infections.^14^ While many hospitals in low-income settings are not able to routinely perform surveillance of resistant patterns, yet the little evidence that does exist suggests an accelerating incidence of antibiotic-resistant SSIs.^15^ Patients with antibiotic-resistant infections have a higher risk of mortality and morbidity, and require more healthcare resources.^16^ Currently, few data exist describing the international epidemiology of SSIs, the causative organisms or incidence of antimicrobial drug resistance. Investigating the diagnosis and treatment of SSIs is an urgent global health priority, with important implications for patients, clinicians and policymakers.

### Primary aims

The primary aim is to determine the incidence of SSI following elective and emergency gastrointestinal surgery across low, middle and high Human Development Index (HDI) countries.

### Secondary aims

The secondary aims include describing the organisms causing SSIs, the incidence of antibiotic-resistant pathogens and the microbiological tests used to identify them. The impact of the method of 30-day follow-up on these outcomes, where performed, will also be analysed.

## Methods

### Study design

This is a multicentre, international, prospective, observational cohort study of all consecutive patients undergoing elective or emergency gastrointestinal surgery over a 14-day period. Individual collaborators are free to choose any 14-day period within the 6-month study period to collect data. The study will run from 4 January 2016 to 31 July (with 30-day follow-up of the last data collection period finishing on 30 August 2016). This ‘snapshot’ study design is a validated model that has been delivered successfully in previous studies.^6 17 18^

### The GlobalSurg network

GlobalSurg (http://globalsurg.org/) is an international research collaborative, fostering regional, national and international surgical networks. The collaborative model used has previously been described elsewhere^19^ and has already facilitated one multicentre, international, prospective cohort study.^20^ GlobalSurg is run by the Surgical Research Gateway (SuRG) Foundation (http://surgfoundation.org/; registered charity number 1159898), in collaboration with the University of Birmingham and University of Edinburgh. The objective of the charity is to advance the education of medical students and doctors in surgical science, clinical research and audit methods by promoting participation in collaborative clinical research and audit studies.

### Study setting

Any surgical unit providing emergency or elective surgery worldwide is eligible to participate. Included centres must capture all consecutive patients and ensure data collection is >95% complete. Centres with >5% missing data, when including all possible data points, will be excluded from the final analysis and removed from authorship. The minimum number of patients that must be recruited is 1. Multiple teams covering different non-overlapping time periods at each hospital are encouraged.

### Patient inclusion and exclusion criteria

Patients of all ages (adult and paediatric) undergoing elective, semielective or emergency gastrointestinal resection, cholecystectomy or appendicectomy are eligible to enter (box 1). Any operative approach can be used. Operations with a primary indication classified as vascular surgery, gynaecology, urology or transplantation should be excluded.Box 1Patient inclusion and exclusion criteriaInclusion criteriaPatients of all ages (adult and paediatric)Consecutive patients during a chosen 14-day study periodUndergoing emergency or elective gastrointestinal resection, cholecystectomy and appendicectomyIncludes open, laparoscopic, laparoscopic converted and robotic casesPrimary indication of trauma should be includedHernia repair with bowel resection should be includedExclusion criteriaOperations with a primary indication classified as vascular surgery, gynaecology, urology or transplantationCaesarean sectionsWhipple procedureSimple hernia repair

Emergency procedures are defined as unplanned operations and include reoperations after previous procedures. Semielective procedures are defined as procedures planned on the background of the patient being discharged after an emergency admission in the past and is currently admitted for surgery. Gastrointestinal resection is defined as a complete transection and removal of a segment of the oesophagus, stomach, small bowel, colon or rectum.

Each individual patient should be included once into the study. Patients who return to theatre due to complications following earlier surgery can only be included if the index procedure is not already included.

### Outcome measures

The primary outcome measure is the incidence of superficial or deep incisional SSI within 30 days of surgery involving any of the operative incisions made. This measure adopts the definitions within the 2008 Centre for Disease Control and Prevention^21^ definitions of SSI (box 2). Where it is unfeasible to follow-up the patients after discharge for 30 days postoperatively, in-hospital SSI incidence will be used as a proxy measure.Box 2Centre for Disease Control and Prevention (CDC) criteria for surgical site infection (SSI)^21^
CDC criteria for SSI require the patient to have at least one of the following:Purulent drainage from the superficial or deep (fascia or muscle) incision but not from within the organ/space component of the surgical siteAt least one of the following: pain or tenderness; localised swelling; redness; heat; fever and the incision is opened deliberately or spontaneously dehiscesAbscess within the wound (clinical, histopathological or radiological detection)

The secondary outcomes that will be derived from this study include:a description of the global variation in organisms causing SSI (including use of microbiological tests);the incidence of antibiotic-resistant pathogens detected in patients with SSI;30-day POMR;30-day postoperative reintervention rate;assessing how difference in SSI rates varies based on the method by which patients are followed up.

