### Investigators

The study will be undertaken by investigators around the world who will be responsible for disseminating the protocol at their individual site, ensuring appropriate study approvals are in place and collecting and uploading data to an online REDCap database. A central study writing committee compromising of an internationally representative group of healthcare professionals will be responsible for data analysis, final manuscript drafting and submission. Individuals will be required to register their unit via the REDCap system and will be required to complete two training modules prior to starting.

Countries with multiple sites will be assigned a country lead, who will be responsible for coordinating multiple teams across sites to ensure duplication of data does not occur. Each hospital will have a primary local investigator who will act as guarantor of data. A maximum of three local investigators can cover each 2-week data collection period. They will be responsible for gaining local audit, service evaluation or research ethics approval as appropriate to their institution. Investigators should also create clear mechanisms to identify and include all eligible patients, which involves daily review of operating logbooks, emergency admission lists and team handover lists. They should identify clear pathways to accurately collect baseline and follow-up data and be proactive in identifying postoperative events within the normal limits of follow-up.

Local arrangements for follow-up may include daily review of the patient and notes during admission and before discharge in order to identify in-hospital SSIs, reviewing patient status in outpatient clinics or via telephone interview at 30 days (if this normal practice), checking hospital notes (paper or electronic) and looking at handover lists. All investigators will be listed as collaborators on resulting publications.

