### Statistical analysis and power calculation

Identification of hospital or surgeon-specific performance will not be reported. Variation in outcome across different contexts will be tested using the HDI^24^ (a composite statistic of life expectancy, education and income indices). Following analysis, centre-specific SSI rates will be fed back to participants. Hierarchical logistic regression multivariate analysis will be used to adjust the influence of HDI on SSI rates for confounding patient and disease variables. We will subgroup patients according to operative procedure for the purpose of analysis.

An appropriate sample size is difficult to calculate in this setting as there is a lack of previous study data to indicate the incidence of SSIs internationally. The previous GlobalSurg study recruited 10 745 patients using the same methodology.^25^Although the inclusion criterion for this study is different, we expect to achieve a similar number of patients. Based on the findings from GlobalSurg 1, this number will provide adequate power to show a minimum difference from 7% to 10% in SSI rate between two groups (80% power at 5% alpha requires a sample size of 1350 patients).

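### The primary SSI endpoint mixes a 30-day window with an in-hospital window, and nothing in the stated HDI comparison separates infection risk from follow-up

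*Protocol article*

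**What the plan says.** Under Outcome measures, the primary outcome is the "incidence of superficial or deep incisional SSI within 30 days of surgery". The same paragraph then sets a substitution rule: "Where it is unfeasible to follow-up the patients after discharge for 30 days postoperatively", "in-hospital SSI incidence will be used as a proxy measure". It gives no criterion for when follow-up counts as unfeasible.

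The Investigators section leaves follow-up to local arrangements. These may include review in clinic or "via telephone interview at 30 days (if this normal practice".

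The primary aim is to describe SSI incidence "across low, middle and high Human Development Index (HDI) countries". Under Statistical analysis and power calculation, a hierarchical logistic regression is to "adjust the influence of HDI on SSI rates for confounding patient and disease variables". Follow-up is not mentioned there.

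The article does recognise that follow-up matters. Secondary aims includes the impact of the 30-day follow-up method, and the list of secondary outcomes includes "assessing how difference in SSI rates varies based on the method by which patients are followed up". Table 1 records SSI before discharge, SSI at 30 days (with a separate response for patients not assessed after discharge), how follow-up was achieved, and length of postoperative stay.

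**The concern.** An SSI that first appears after discharge can be counted where patients are reviewed to day 30. It cannot be counted where the in-hospital proxy applies. If the share of patients on the proxy is similar in every HDI group, all rates are understated but the comparison is largely preserved. If the share differs by HDI, the comparison mixes infection risk with intensity of follow-up.

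Such a difference is plausible: follow-up depends on local feasibility and usual practice, and the Discussion expects low-resource centres to take part. Follow-up status is neither a patient nor a disease variable, so the adjustment described does not reach it. A hierarchical structure does not remove a centre-level ascertainment difference that is correlated with HDI. A larger sample does not remove it either.

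At stake is the interpretation of the primary result. The feedback of centre-specific rates is also affected, because a centre that follows its patients diligently would look worse than one that does not.

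**Working it through.** **The plan's own figure.** The article states 1350 patients for 7% versus 10% at 80% power and 5% alpha. For a two-sided test with pooled variance under the null and no continuity correction:

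n per group = [1.960 × √(2 × 0.085 × 0.915) + 0.842 × √(0.07 × 0.93 + 0.10 × 0.90)]² / 0.03² = 1356.

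So 1350 is reproduced closely as a number per group, with power of 80%. The 7% versus 10% contrast is used below as the planning difference. Its true odds ratio (OR) is (0.10/0.90)/(0.07/0.93) = 1.48.

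**Model for the mixed endpoint.** Observed rate = p × [1 − (1 − f) × s], where
- p is the true 30-day SSI rate;
- f is the share of patients followed to day 30;
- s is the share of 30-day SSIs that first appear after discharge.

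The documents give neither f nor s. Both are assumptions here: s from 30% to 60%, and f = 90% in high HDI against 50% in low HDI. The model also assumes that s is the same in both settings and that being followed is unrelated to infection.

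At s = 30%, the multipliers are 1 − 0.1 × 0.3 = 0.97 (high) and 1 − 0.5 × 0.3 = 0.85 (low). At s = 60% they are 0.94 and 0.70.

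| s | Equal true 12%: observed high vs low (OR) | True 7% vs 10%: observed high vs low (OR) |
|---|---|---|
| 30% | 11.6% vs 10.2% (0.86) | 6.8% vs 8.5% (1.28) |
| 50% | 11.4% vs 9.0% (0.77) | 6.7% vs 7.5% (1.14) |
| 60% | 11.3% vs 8.4% (0.72) | 6.6% vs 7.0% (1.07) |

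**Power.** With 1350 per group, a true 7% versus 10% and the same 90% versus 50% follow-up, power falls from 80% to 54%, 31% or 14% at s = 20%, 35% or 50%. Clustering is ignored.

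**Direction.** Reverse the follow-up pattern (50% high, 90% low). At s = 30%, a true 7% versus 10% becomes 0.07 × 0.85 = 5.95% versus 0.10 × 0.97 = 9.70%, OR 1.70. At s = 60% it becomes 4.9% versus 9.4%, OR 2.01. The contrast is exaggerated.

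**Equal follow-up.** With 70% followed in both groups, the OR stays at about 1.47 for s from 20% to 60%. The distortion comes from the difference in follow-up, not from incomplete follow-up as such.

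**A large gradient.** Take the GlobalSurg 1 rates in the Introduction (7.4% high income, 20.0% low income; income groups rather than HDI) as true. At s = 60% with 90% versus 50% followed, they become 0.074 × 0.94 = 6.96% and 0.20 × 0.70 = 14.0%. The OR falls from 3.13 to 2.18: attenuated, not lost.

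**Where reversal would start.** For a true 7% versus 10% with 90% versus 50% followed, reversal needs 0.10 × (1 − 0.5s) < 0.07 × (1 − 0.1s), that is s > 0.03/0.043 = 70%. This is outside the assumed range. With 90% versus 30% followed, it needs s > 0.03/0.063 = 48%.

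**The case against.** The strongest reply has four parts.

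1. This is a condensed article. Naming patient and disease variables does not close the covariate list, and an analysis plan not shown here may add follow-up status. That is fair, and the silence on covariates would not be a finding by itself. However, the article does fix the substitution rule for the primary outcome and states what the HDI adjustment is for. Followed as written, the two windows enter the primary comparison together.

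2. The authors saw the issue. They made follow-up method a secondary aim and collect the fields needed to examine it. This stands, and it means the problem need not go unseen. But nothing says that this analysis changes, restricts or repeats the primary HDI comparison. The rule on missing data need not catch it, because not being assessed after discharge is a permitted response. The validation covers case completeness and local data collection methods, not missed post-discharge infections.

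3. HDI comparisons are declared hypothesis generating, and using only usual-care data is a deliberate pragmatic choice. Both are true and limit the consequences. Neither makes incidences measured over different windows comparable.

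4. The magnitude is assumed. This is correct.

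A reader might also infer that unassessed patients are recorded as having no SSI. Table 1 keeps them in a separate category, and the article does not say how the analysis codes them. The proxy rule implies only that their later infections are not counted.

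**Conclusion.** The point holds as a defect in how the primary endpoint is fixed. Two observation windows share one label, their mix depends on local practice and may differ by HDI, and neither the stated adjustment nor the secondary analysis corrects the primary contrast.

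The figures show what could happen under assumed follow-up and post-discharge shares; they are not an estimate of what will happen. A modest gradient such as 7% versus 10% could be largely masked or considerably exaggerated, and a spurious OR of 0.86 to 0.72 could arise where there is no true difference.

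A reader might infer that the plan will hide or reverse the HDI gradient. The documents do not support that. They do not say that low-HDI centres follow up less, the bias could run either way, and no scenario in the 90% versus 50% range reverses a true gradient. Reversal takes more extreme assumptions, for which the article offers no basis. A gradient as large as that in GlobalSurg 1 would remain visible at an OR of about 2.2.

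**What to change.** Do not rest the HDI comparison on the pooled composite alone. From fields already in Table 1, report by HDI group:
- (a) pre-discharge SSI in all patients, with length of stay shown alongside;
- (b) 30-day SSI in patients with known day-30 status, with the share assessed in each HDI group.

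Repeat the hierarchical HDI model twice: with follow-up status (30-day versus in-hospital only) as a covariate, and restricted to assessed patients.

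Inverse-probability weighting or multiple imputation may be added as a sensitivity analysis, with its limits stated. Either assumes that post-discharge status is missing at random, and a centre that follows nobody has no assessed patients to weight, so its estimate must be borrowed from elsewhere. The restricted analysis has its own limit: it overstates incidence if infected patients return more often. This is why (a) and (b) belong together.

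Do not use length of stay as a routine covariate. The Introduction says that SSI lengthens stay, so adjusting for it would condition on a consequence of the outcome.

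The cost is some extra wording and programming, with no new data. Intervals for (b) will be wider because fewer patients contribute. Event rates for (a) will be lower: if half of SSIs appeared after discharge in every setting, 7% versus 10% would become 3.5% versus 5.0% and need 2838 per group instead of 1356.

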**Surgical site infection**	
Prior to discharge	Yes, No
At 30 days after surgery	Yes, No, Not assessed after discharge
	*If yes:* Was a wound swab sent for microbiological culture: Yes, No—but available in this centre, No—not available in this centre
	*If yes:* How was this treated: operative drainage, wound opened outside of operating theatre, antibiotics (tick all that apply)
What bacteria, if any, were identified?	None, *Staphylococcus aureus*, Coliform, Anaerobe, Other (five tick boxes)
	*If yes*: Sensitivity: sensitive to antibiotic prophylaxis given; resistant to antibiotic prophylaxis given; sensitivities not tested—but available in this centre; sensitivities not tested—not available in this centre
30-day unexpected reintervention. Record the most serious reintervention	Yes—surgical, Yes—endoscopic, Yes—interventional radiology, No
30-day mortality	Dead, Alive, Unknown. *If died:* postoperative day of death
30-day intra-abdominal/pelvic abscess (CT, ultrasound or clinical (including reoperation) evidence of intra-abdominal or pelvic abscess)	Yes, No
Other hospital-acquired infection (treated with or without antibiotics)	Yes—urinary tract infection, Yes—pneumonia, Yes—central venous line infection, Yes—peripheral line infection, Yes—other, No
How was 30-day follow-up status achieved? (all applicable)	Still an inpatient, Clinic review, Telephone review, Community/home review, Discharged before 30 days and not contacted again

ASA, American Society of Anaesthesiologists; GI, gastrointestinal; NSAID, non-steroidal anti-inflammatory drug; PCV, packed cell volume.

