SSIs have been shown to increase costs by an average of US$20 842 in high-income countries, which significantly burden healthcare systems.^29^ Within low-income countries, healthcare-associated infections have been estimated to have an increased incidence.^30^ This can result in an increased length of stay of an average 9.7 days longer and has further knock-on effects to dependants which are more profound in the low-income setting.^29^ To help address this fiscal disparity, this project will inform future service-level quality improvement programmes. When regular audits of pathogens and antibiotic prescribing are undertaken, redundant antibiotic use is reduced.^31 32^ With feedback of baseline SSI rates to participating centres, collaborators have the opportunity to appraise their current practice against a global standard. Surgeons will be able to implement interventions to improve service provision prior to a reaudit, 1 year in the future. With the savings made from the implementation of prevention programmes being 11 times greater on average than costs,^33^ these programmes will help reduce fiscal burden to patients and public health systems.

Many important determinants of a high burden of SSI in developing countries have not been identified.^5^ This study will be able to identify an association between SSIs and various risk factors, however, due to its observational nature, it will not be able to prove causality. Therefore, data points collected have been included with a plausible relationship with SSIs. The number of data collection points has been kept short in order to maximise data completeness and accuracy and minimise investigator workload.

Finally, this study will continue to strengthen the GlobalSurg network, developing capacity for research in LMICs.^34^ For the many research-naive centres worldwide, participation in this project could instil a culture of clinical effectiveness into routine clinical practice. This study will ultimately provide the basis for a global multicentre randomised controlled trial, aimed at reducing the burden of SSI and its attributed morbidity and mortality.

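### SSI rates by follow-up method cannot be read as the impact of that method: SSI can influence the category recorded, and permitted notes review has no category

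*Protocol article*

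**What the plan says.** Under Outcome measures, the last secondary outcome is "assessing how difference in SSI rates varies based on the method by which patients are followed up". Secondary aims puts it as an effect: "The impact of the method of 30-day follow-up on these outcomes, where performed, will also be analysed".

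The only item in Table 1 that records the method is "How was 30-day follow-up status achieved? (all applicable", with the options "Still an inpatient, Clinic review, Telephone review, Community/home review, Discharged before 30 days and not contacted again". It is filled in for each patient, describes what had happened by day 30, and allows more than one answer. Table 1 has no field for a centre's planned or usual follow-up.

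The Investigators section describes what local follow-up may consist of. It includes "reviewing patient status in outpatient clinics or via telephone interview at 30 days (if this normal practice" and also "checking hospital notes (paper or electronic) and looking at handover lists".

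On length of stay, the Introduction states that "SSIs cause pain and discomfort, increase hospital stay". The Discussion, speaking of healthcare-associated infection, gives "an increased length of stay of an average 9.7 days longer".

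**The concern.** The aim is to learn how far the measured SSI rate depends on how patients were followed up. That requires a method that does not itself depend on whether the patient had an SSI, and that is recorded correctly. The Table 1 item falls short on both counts.

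- **SSI can influence the category.** Still being an inpatient is a state rather than a method, and on the article's own statement SSI lengthens stay. By inference, a wound problem may also bring a patient back to clinic unplanned, while a well patient is left uncontacted.
- **One permitted route cannot be recorded.** A discharged patient followed only through notes fits, at best, the not-contacted option, together with patients about whom nothing was learned after discharge. This is misclassification, a separate defect from the first.

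Because several answers may be ticked, the groups can also overlap. What is at stake is the interpretation of one named secondary outcome; the definition of the primary outcome is not affected.

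**Working it through.** The article gives no figure for this comparison. Its one design figure, 1350 patients for 7% versus 10% SSI, is reproduced as a per-group number (1356, two-sided 5%, 80% power, no continuity correction). Nothing below depends on it.

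**Check 1: how large a difference can arise when every method detects SSI equally well?**

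Inputs:
- p = SSI rate. Rates of 7.4%, 14.4% and 20.0% come from the earlier cohort described in the Introduction.
- q0 = probability of being recorded in category M without SSI. Assumed 5% or 30%.
- r = factor by which SSI multiplies that probability. Assumed 1 to 3; the documents do not give it.

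Formulas (Bayes' rule):
- Rate in M = p·r·q0 / [p·r·q0 + (1 − p)·q0]
- Rate outside M = p·(1 − r·q0) / [p·(1 − r·q0) + (1 − p)·(1 − q0)]

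Example with p = 0.144, q0 = 0.05, r = 2:
- In M: 0.0144 / (0.0144 + 0.0428) = 25.2%
- Outside M: 0.1296 / (0.1296 + 0.8132) = 13.7%
- Risk ratio 1.83, although detection is identical

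Results at p = 14.4%:

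| r | Rate in M | Outside M, q0 = 5% | Risk ratio | Outside M, q0 = 30% | Risk ratio |
|---|---|---|---|---|---|
| 1 | 14.4% | 14.4% | 1.00 | 14.4% | 1.00 |
| 1.25 | 17.4% | 14.2% | 1.22 | 13.1% | 1.33 |
| 1.5 | 20.1% | 14.1% | 1.43 | 11.7% | 1.73 |
| 2 | 25.2% | 13.7% | 1.83 | 8.8% | 2.87 |
| 3 | 33.5% | 13.1% | 2.56 | 2.3% | 14.29 |

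At r = 2, the risk ratio is 1.96 (q0 = 5%) or 3.16 (q0 = 30%) for p = 7.4%, and 1.74 or 2.67 for p = 20.0%. The last row with q0 = 30% is extreme: it puts 90% of all patients with SSI in M.

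**Check 2: what does the missing notes-review option do?**

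Assume 14.4% true SSI, 50% of SSIs detected in patients with no assessment after discharge, 70% to 90% detected by notes review, and half of the not-contacted group in fact reviewed by notes.

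- No notes-reviewed patients in the group: 0.144 × 0.50 = 7.2%
- Half reviewed, 70% detection: 0.144 × (0.5 × 0.50 + 0.5 × 0.70) = 8.6%
- Half reviewed, 90% detection: 0.144 × (0.5 × 0.50 + 0.5 × 0.90) = 10.1%

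The rate in the mixed group then describes neither kind of patient.

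**The case against.** The strongest reply is that the centre, not the patient's wound, sets the method. The Investigators section ties clinic and telephone review to normal practice, and Outcome measures ties absent follow-up to feasibility. If that were the whole story, r = 1 and this bias vanishes. The point stands as a limit on the claim. A reader might infer that an SSI determines the method and that the comparison will simply display reverse causation. The documents do not support this: they show only that SSI can influence at least one category, and genuine differences in detection will be mixed in.

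Second, the article gives this comparison one line, and the model may be set out in an analysis plan not shown. That is fair as to the model. But the field and its options are fixed in Table 1, and an analysis plan cannot create a category that was not collected. Partial recovery is possible, because the 30-day SSI item has its own answer for patients not assessed after discharge. The article does not say, however, whether notes review counts as assessment.

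Third, the still-inpatient option is separate and can be set aside without new data. This is correct, and it is why that part of the remedy is cheap.

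Fourth, it might be said that patients who died lack a category. The 30-day mortality item already identifies them, so this is not a defect.

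Finally, a reader might infer that the result would distort the comparison across Human Development Index groups. No section says it will be used in that way, and the article already describes that comparison as hypothesis generating.

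**Conclusion.** The concern holds in limited form. The difference in SSI rate between recorded follow-up categories cannot be interpreted as the impact of follow-up method, because SSI can affect the category and one permitted route cannot be recorded. For the still-inpatient option, the first reason rests on the article's own statement; for unplanned clinic review it is inference.

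The size cannot be fixed from the documents. At 14.4% SSI with 5% of patients without SSI in the category, the spurious risk ratio runs from 1.00 (local practice alone) to 2.56 (SSI triples the chance of that category); larger categories give larger values. These figures illustrate assumed attendance patterns and do not estimate the bias in this study. The equal-detection assumption also cannot apply to patients never contacted, for whom a real shortfall in detection is expected and is what the aim sets out to study.

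**What to change.** 1. Add one option to the Table 1 follow-up item for review of hospital notes or the electronic record only. If data collection has closed, say that the not-contacted group is a mixture, and cross-tabulate it with the 30-day SSI item.
2. Restrict the between-method comparison to patients discharged before day 30, and report those still in hospital descriptively only.
3. Add a supporting analysis that enters the centre's usual follow-up practice in the hierarchical model.
4. Describe the result as an association between method and recorded SSI rate, in place of an impact.

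No option for death is needed.

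Cost: one extra field option and a few sentences of analysis text. The restricted comparison describes discharged patients only, and it still leaves any effect of SSI on unplanned clinic review. The centre-level contrast is less precise, is unstable where a centre contributes few patients (Study setting allows one), and may be confounded with setting. For these reasons it should be supporting rather than the main analysis.
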